### Participants

Patients are aged 18 to 65 years and have chronic musculoskeletal disorders, usually back pain. They have approval for rehabilitation either in an own rehabilitation institution of the Federal GPI or an institution that is leadingly occupied by the Federal GPI. Patients have requested rehabilitation because of health-related restrictions of work ability. Need for rehabilitation was acknowledged by a registered doctor and approved by the Federal GPI. Allocation to CMR and WMR is primarily decided by the socio-medical service of the Federal GPI. The socio-medical service may consider the findings of standardized screening which is usually part of the application documents and estimates the risk of not returning to work [11].

### Sample size estimation

We expect to find small mean differences between WMR and CMR in primary outcomes. For three months, of about 18,000 insured patients with permission for a musculoskeletal rehabilitation program 15,000 will receive CMR and 3,000 will receive WMR. We expect a participation rate of 40 %, i.e. 7,200 patients (6,000 CMR, 1,200 WMR) at baseline. At the 10-month follow-up, we expect a dropout rate of 25 %, i.e. 900 patients with WMR and 4,500 CMR left. Using a one-to-one match without replacement, 1,800 patients (900 WMR, 900 CMR) will be analyzed. Assuming a number of clusters (departments) *k* = 256 (with 176 departments providing CMR and 80 departments providing additionally WMR), a cluster size of *m* = 7.0, an intracluster correlation of rho = 0.05, a power of 0.80 and a Bonferroni corrected *p*-value = 0.016, an effect of SMD = 0.175 can be detected (Fig. 1).

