### Statistical analysis

#### Propensity score matching

Patients of WMR and CMR will be matched by propensity scores to achieve balanced sample characteristics and to calculate unbiased estimates of relative effectiveness [22, 48–54]. The propensity score is the conditional probability of receiving the treatment under evaluation (i.e. WMR) given the vector of observed background variables. Matching by propensity scores enables balanced characteristics of the treated and the untreated sample if there is sufficient overlap of the propensity scores of both groups. Compared with a conventional direct matching procedure the problem of multidimensionality in finding a corresponding control, for instance related to age, sex, sickness absence duration, pain, depression and others, is thereby reduced to one dimension only.

The propensity score will be estimated by a logistic regression model including all variables that are associated with the treatment allocation. For every WMR participant a patient with a similar propensity score will be selected from the larger pool of CMR patients. Resampling will be realized without replacement. If necessary to achieve balanced data, a caliper of one-quarter of the propensity score during resampling will be used. For sensitivity analysis, additional matching schemes will be tested (with and without replacement, different calipers, varied number of controls). As an indicator of the bias before and after matching owed to differences related to the observed sample characteristics the standardized percentage bias will be calculated. This is the difference of the sample means in cases and controls relative to the square root of the average of the sample variances in both groups [55]. Multiple imputations will be used to fill in missing data before estimation of the propensity score. The propensity scores for each record will be averaged across the completed datasets, and propensity score matching will be performed with these averaged scores [56].

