#### Multilevel regression analyses

Analyses of treatment effects in propensity score matched samples can use the same statistical methods as those used in experimental studies [48, 49]. Multilevel regression analyses will be used to account for dependencies in the data [57, 58]. Individual patient data will be conceptualized as level-1 parameters and the rehabilitation department as a level-2 variable. All models will include the treatment variable (WMR vs. CMR), the baseline score of the respective outcome measure and a random intercept which reflects the rehabilitation department. For the primary outcomes, p-value will be fixed at 0.016 (Bonferroni corrected for three outcomes). For the secondary outcomes, p-value will be fixed at 0.05. Linear models will be used for continuous outcomes and logistic models for binary outcomes.

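### The sample size section matches and analyses only patients still in the study at 10 months, and nothing else stated in the article deals with selection through dropout

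*Protocol article*

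**What the plan says.** All references are to the protocol article.

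- **Sample size estimation.** The starting point is "We expect a participation rate of 40 %, i.e. 7,200 patients (6,000 CMR, 1,200 WMR) at baseline". Dropout follows: "At the 10-month follow-up, we expect a dropout rate of 25 %, i.e. 900 patients with WMR and 4,500 CMR left". Matching comes after that: "Using a one-to-one match without replacement, 1,800 patients (900 WMR, 900 CMR) will be analyzed".
- **Propensity score matching.** Imputation is mentioned once: "Multiple imputations will be used to fill in missing data before estimation of the propensity score". The completed datasets have one described use: "The propensity scores for each record will be averaged across the completed datasets, and propensity score matching will be performed with these averaged scores". The sensitivity analyses listed there change replacement, calipers and the number of controls.
- **Multilevel regression analyses.** The outcome model is given as "All models will include the treatment variable (WMR vs. CMR), the baseline score of the respective outcome measure and a random intercept which reflects the" department. It has no repeated patient measures, so the 3-month values do not enter the 10-month comparison.
- **Primary outcomes and Table 2.** Sick leave duration, stable return to work and work ability are judged at 10 months and also collected at 3 months. None of the three is listed as coming from the pension-insurance accounts.
- **Study design and Recruitment.** Nobody is blinded. Follow-up questionnaires are mailed, with one repeat mailing. Permission to link administrative records is sought at recruitment.

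**The concern.** In the order given, the comparison groups are formed from people selected by an event after treatment, namely still being in the study at 10 months. The article says that matched samples can be analysed like experiments and calls the resulting estimates unbiased. In an experiment, however, the groups are fixed before follow-up. Matching balances baseline characteristics among those who remain. It does not balance what happened between discharge and month 10, such as early return to work, relapse or satisfaction with the programme. Any of these may affect both the decision to return a questionnaire and the answer given.

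A respondent-only comparison is sound if, given treatment and the covariates used, response is unrelated to the outcome. If that relation exists and differs between the programmes, even a perfect baseline match leaves bias. The planned effect is small, so a modest bias would count. The 3-month outcomes and linked records could explain part of the non-response, but the described analysis of the primary outcomes does not draw on them.

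**Working it through.** **1. Patient flow (Sample size estimation).**

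- WMR: 1,200 × 0.75 = 900. CMR: 6,000 × 0.75 = 4,500.
- 1:1 match: 900 + 900 = 1,800, which equals the number said to be analysed.
- Matching all WMR baseline participants would give up to 1,200 + 1,200 = 2,400. This is an upper limit, because some of the 25% may be patients who never start rehabilitation, and the article does not split the figure.
- If matching came first and 25% then dropped out independently, 900 per group would still respond, but only 1,200 × 0.75² = 675 pairs would be complete.

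The stated 1,800 therefore corresponds to matching those who remain.

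**2. The plan's own detectable effect.** Inputs from the same section: m = 7.0, rho = 0.05, power 0.80, alpha 0.016. Sidedness is not stated.

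- Design effect = 1 + (7.0 − 1) × 0.05 = 1.30.
- SMD = (2.409 + 0.842) × √(2 × 1.30 / 900) = 3.251 × 0.0537 = 0.1747.

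This reproduces the stated 0.175 with a two-sided test (one-sided gives 0.160). The figure is right for 900 per group.

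**3. Bias of a respondent-only mean difference.** Let d be the dropout share and g the respondent minus non-respondent mean in SD units, after matching and baseline adjustment. The respondent mean exceeds the full-group mean by d × g, so

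bias = d(WMR) × g(WMR) − d(CMR) × g(CMR).

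The article gives d = 0.25 in both groups and no value for g. Hence bias = 0.25 × [g(WMR) − g(CMR)]. Type I error uses the standard error 0.0537 from step 2.

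| Assumed difference in g (SD) | Bias in SMD | Share of 0.175 | Type I error (nominal 1.6%) |
|---|---|---|---|
| 0 | 0 | 0% | 1.6% |
| 0.1 | 0.025 | 14% | 2.8% |
| 0.2 | 0.050 | 29% | 7.0% |
| 0.3 | 0.075 | 43% | 15.6% |
| 0.5 | 0.125 | 71% | 46.7% |

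If dropout differed instead (assumed 20% v 30%) with a common gap of 0.2 to 0.8 SD, the bias would be 0.10 × 0.2 = 0.02 to 0.10 × 0.8 = 0.08 in size.

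**4. Stable return to work.** This outcome is binary and modelled by logistic regression, so the SD figures do not carry over. If response depends on the outcome alone, in the same way in both groups, the odds ratio is preserved.

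**5. Is the selection offset elsewhere?** The imputation is placed before the propensity score and serves to average scores for a single match. The outcome model has no 3-month term, and the sensitivity analyses concern matching. None of the three addresses missing 10-month outcomes.

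**The case against.** The strongest reply is that the quoted sentences are planning arithmetic. Reducing n for expected dropout is routine and need not define the analysis set. The matching section speaks of every WMR participant, not every respondent, and neither analysis section excludes anyone for non-response. The flow figure is not shown, and a fuller analysis plan may deal with missing outcomes.

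Part of this stands. The order of dropout and matching appears only in the sample size section, and the mere absence of a missing-outcome method from an article would be no finding. But that section goes beyond reducing a number: it places the match after dropout and says who will be analysed.

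Several stronger readings are tempting and are not supported:

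- **That outcome imputation is ruled out.** The article fixes when imputation happens, not which variables are imputed. Restriction to propensity variables is a natural inference, not a stated rule.
- **That the pension records go unused.** They supply income and benefit duration as secondary outcomes. What is missing is a described role for them in handling missing primary outcomes.
- **That the primary outcomes will be biased by a known amount.** The article expects equal dropout, and no gap is given. With equal dropout and equal gaps the bias in a mean difference is zero.
- **That dropout must depend on baseline covariates alone.** The condition is weaker: response must be unrelated to the outcome given treatment and covariates, so dropout may differ by group.

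It is also fair to say that imputation helps only as far as observed data explain non-response.

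**Conclusion.** The concern holds as a weakness in a stated plan that should be changed. As written, the article expects to match and analyse those remaining at 10 months, and no other described step counters selection by response. Because selection follows treatment and the primary outcomes are unblinded self-reports, baseline matching does not remove it.

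The size and direction of bias cannot be derived from the documents. The shift of 0.05 in SMD rests on an assumed 0.2 SD between-group difference in the respondent/non-respondent gap at the article's 25% dropout, and applies to the continuous outcomes. The detectable SMD of 0.175 is correct for 900 per group and is not in dispute.

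**What to change.** 1. State in the analysis section that the matched sample is formed from all baseline participants who start rehabilitation, whether or not they later respond.
2. In that sample, multiply impute missing 10-month primary outcomes and combine results with Rubin's rules, or weight respondents by the inverse probability of response. Use treatment, the propensity covariates, the 3-month outcomes, department and, where linkage is permitted, the pension-insurance records. The 3-month sick leave answer should be especially useful: it counts weeks since discharge and so covers part of the 10-month total.
3. Keep the matched respondent-only analysis as a sensitivity analysis, and report response by group.

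The cost is a change of wording and modest extra analysis, with no new data. Two limits should be acknowledged. The approach relies on outcomes being missing at random given these data, so response driven by unobserved 10-month status would not be fully corrected. Many matched pairs will also have an incomplete member (about 675 of 1,200 complete under independent dropout), so the analysis should not require complete pairs; the planned multilevel model, as described, does not.

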**Fig. 1 Fig1:**
[figure not shown]
Flow of participants

### Recruitment

Participants with chronic musculoskeletal complaints whose request for rehabilitation was approved will be contacted by postal mail. Mails will be delivered in three waves at four-week intervals. All persons whose rehabilitation measure was approved within the previous four weeks will be contacted in each wave. The letter contains information about the study with the request to participate and the baseline questionnaire. The questionnaire contains no personal data but a unique study identifier. No personal data (e.g. name and address) will be submitted or published by the Federal GPI. One week after the initial postal contact a reminder will be sent to all potential participants. All participants will be thanked and reminded to participate if they have not yet done so. By this method, we expect to increase participant enrolment in order to reach our estimated target sample size and to strengthen external validity. Informed consent is assumed if patients complete their questionnaire and send the questionnaire to the research team. Additionally, participants will be asked to give permission to use administrative data from their pension insurance accounts and to link these data with the questionnaire data.

At the three- and ten-month follow-up participants who complete the baseline questionnaire will receive follow-up questionnaires from the Federal GPI (Table 1). Three weeks later the questionnaire will be sent again with a reminder to all participants who have not completed the questionnaire yet.

**Table 1 Tab1:**
[figure not shown]
Schedule of enrolment, interventions, and assessments

### Data management

Questionnaires will be scanned and verified by an electronic data capture system and exported to statistical software packages for further analysis. Scanning and verifying will be done by trained research assistants. They will check electronically processed data item by item and compare imported data with the original questionnaire data. Administrative data will be extracted by the Federal GPI. Personal data will be removed and replaced by the unique study identifier. Data will be transferred to the principal investigator (MB). Finally, questionnaire and administrative data can be linked by the unique study identifier.

Data management will be done by the authors of the protocol. Data access is limited to the authors and the research assistants of the research team.

### Outcomes and other measures

This study will assess three primary outcomes as well as secondary outcomes, moderator variables and variables for propensity score matching. Outcomes and other measures will be assessed with patient questionnaires or will be extracted from administrative records (i.e. individual pension insurance accounts) provided by the Federal GPI. A complete list of all measured constructs, measurement points and expected scaling is shown in Table 2.

**Table 2 Tab2:** Measures, assessment, expected scaling and measurement occasions

Outcome	Source and reference	Scaling	Baseline	3-month follow-up	10-month follow-up
Primary outcomes					
Sick leave duration in weeks	Own development	metric	X	X	X
Stable return to work	Own development	binary	X	X	X
Subjective work ability	WAS [28]	metric	X	X	X
Secondary outcomes					
General health	COPSOQ (1 item) [30, 31]	metric	X	X	X
Physical functioning	IRES-24 [32]	metric	X	X	X
Depression	PHQ-2 [33]	metric/binary	X	X	X
Anxiety	GAD-2 [34]	metric/binary	X	X	X
Pain intensity	CPQ [35, 36]	metric	X	X	X
Pain disability	CPQ [35, 36]	metric	X	X	X
Fear of movement	FABQ [37, 38]	metric	X	X	X
Physical activity	Modified Godin-Scale [39]	metric	X	X	X
Medication use	Own development	nominal	X	X	X
Self-management skills	heiQ [40]	metric	X	X	X
Employment	Own development	binary	X	X	X
Current sickness absence	Own development	binary	X	X	X
Subjective prognosis of employment status	SPE [41]	metric/binary	X	X	X
Implementation of work-related interventions	[19]	metric		X	
Consistency of the work-related strategy	[19]	metric		X	
Work-related benefit	[19]	metric		X	
Treatment satisfaction	CSQ-8 [42]	metric		X	
Income and welfare benefits	GPI accounts	metric	X		X
Therapeutic interventions	GPI accounts	metric			X
Department characteristics	Department survey	metric/nominal			X
Other measures					
Risk scores for not returning to work	SIMBO [11], WS [12]		X		
Somatization	SCL-90-R [43]	metric	X		
Pain generalization	Own development	metric	X		
Psychosocial stress	[44]	metric	X		
Socio-demographic data	Own development	metric/nominal	X		
Size of company	[45]	nominal	X		
Physical job demands	[46]	metric	X		
Effort-reward imbalance	[47]	metric	X		
Overcommitment	[47]	metric	X		
Support by co-workers and supervisors	Own development	metric	X		

Notes: *SCL-90-R* Symptom Check-List-90-R, *SIMBO* Screening-Instrument zur Feststellung des Bedarfs an medizinisch-beruflich orientierten Maßnahmen in der medizinischen Rehabilitation (Screening to assess the need for work-related medical rehabilitation), *COPSOQ* Copenhagen Psychosocial Questionnaire, *CPQ* Chronic Pain Grade Questionnaire, *CSQ*-8 Client Satisfaction Questionnaire, *FABQ* Fear-Avoidance Beliefs Questionnaire, *GAD*-2 Generalized Anxiety Disorder Questionnaire, *heiQ* Health Education Impact Questionnaire, *IRES*-24 Indikatoren des Reha-Status (Indicators for rehabilitation status), *PHQ*-2 Patient Health Questionnaire, *SPE* Subjective prognosis of employment status, *WAS* Work Ability Score, *WS* Würzburger Screening

#### Primary outcomes

The primary outcomes of this study are sick leave duration, stable return to work, and subjective work ability. Evaluation of the effectiveness of WMR relates to the 10-month follow-up. These three outcomes will also be assessed at the three-month follow-up and if appropriate at baseline.

To assess the duration of sick leave, the participants will be asked to report the number of weeks they have been off work for health reasons since discharge from the rehabilitation center. At baseline this question is related to the last 12 months. Stable return to work has been defined in accordance with Kuijer and colleagues [27] as a minimum of four weeks of employment without sick leave. Subjective work ability will be assessed by the Work Ability Score (WAS), which is the first item of the Work Ability Index (WAI) [28]. It compares current subjective work ability with the lifetime best. The 11-point scale ranges from zero (complete incapacity to work) to ten (lifetime’s best work ability). The WAS is highly correlated with the overall WAI score [29].

#### Secondary outcomes

Secondary outcomes cover several dimensions of health, functioning and coping strategies (see below) and will be measured at all three measurement points. At the three-month follow-up, participants will also evaluate how the rehabilitation programs dealt with work-related issues as well as satisfaction with the treatment.

##### General health

One item of the Copenhagen Psychosocial Questionnaire will be used to measure general health. The 11-point scale ranges from zero (worst imaginable health state) to 10 (best imaginable health state) [30, 31].

##### Physical functioning

Physical functioning is measured by eight items of the IRES-24 (German: Indikatoren des Reha-Status) [32], a widely used instrument in rehabilitation research in Germany. All items are measured on a five-point scale. Item values are averaged and rescaled to a range from zero to 10 points, with lower values indicating less functioning.

##### Depression and anxiety

The two-item versions of both the Patient Health Questionnaire (PHQ-2) and the Generalized Anxiety Disorder Questionnaire (GAD-2) will be used to assess depression [33] and anxiety [34]. The PHQ-2 uses the first two items of the PHQ-9 (“little interest or pleasure in doing things,” “feeling down, depressed or hopeless”) while the GAD-2 uses the first two items of the GAD-7 (“feeling nervous, anxious or on edge", “not being able to stop or control worrying”). All items are measured on a four-point scale (0 = not at all, 1 = several days, 2 = more than half of the days, 3 = nearly all days). Sum scores for depression and anxiety range from zero to six points. Additionally, we will determine binary outcomes by categorizing values of >2 as clinically relevant depressive or anxiety disorder.

##### Pain intensity and disability

Six items from the Graded Chronic Pain Scale will be used to assess pain intensity and pain disability [35, 36]. Pain intensity items cover current pain and worst pain in the last four weeks and average pain in the last four weeks. Pain disability is related to interference with daily activities, recreational, social and family activities and work activities. All items are scored from zero to 10 points, with higher scores indicating stronger pain or more disability. Items will be averaged and multiplied by 10. Thus, the composite scores range from zero to 100 points.

##### Fear of movement

Two items of the Fear-Avoidance Beliefs Questionnaire [37] (“My pain was caused by physical activity,” “I should not do physical activities which might make my pain worse”) will be used to assess fear of movement. Like Kent and colleagues [38], we will use scaling from zero (completely disagree) to 10 (completely agree) instead of the original scaling. A composite score is determined by averaging both item scores.

##### Physical activity

A modified version of the Godin Leisure-Time Exercise Questionnaire [39] will be used to assess how often per week and how long per session patients performed light, moderate and strenuous physical exercise. The total physical activity score in minutes per week will be calculated by multiplying the total number of sessions per week (in each domain) by the minutes per session (in each domain). Additionally, a total sum score will be calculated by multiplying the scores of each domain with the metabolic equivalent of tasks (9 = strenuous, 5 = moderate and 3 = light physical exercise).

##### Medication use

Medication used to reduce pain (e.g. Paracetamol), to enhance mood (e.g. Citalopram) or to treat other health complaints will be assessed by three new developed items. Response categories are no, regularly (e.g. daily) and rescue medication.

##### Self-management skills

Self-management skills will be assessed with three items of the scale *Skill and technique acquisition* of the Health Education Impact Questionnaire [40]. The items are measured on a four-point scale (1 = strongly disagree, 2 = disagree, 3 = agree, 4 = strongly agree). The scale score is the unweighted mean of all items, with higher values indicating higher subjective self-management skills.

